# Protocol for the internet-based lifestyle intervention to eradicate obese frailty in prostate cancer survivors (iLIVE) randomized controlled trial: a type I hybrid effectiveness implementation trial

**DOI:** 10.1186/s12885-026-15851-4

**Published:** 2026-03-25

**Keywords:** Obesity, Frailty, Prostatic neoplasms, Intervention, Internet, Randomized controlled trial, Sarcopenia, Older, Diet, Physical activity

## Abstract

**Background:**

Obese frailty is a growing national problem as trends towards aging and obesity converge. This problem is especially acute in men with prostate cancer treated with androgen deprivation therapy (ADT). ADT is the backbone of therapy for advanced prostate cancer, a disease which affects mostly older men. But, ADT accelerates muscle loss and gains in adiposity which threaten physical functioning and quality of life. Diet and resistance training may mitigate obese frailty but have rarely been combined in an accessible delivery format.

**Methods:**

The Internet-Based Lifestyle Intervention to Eradicate Obese Frailty in Prostate Cancer Survivors (iLIVE) Randomized Controlled Trial (RCT) aims to mitigate obese frailty among men with prostate cancer treated with ADT. Participants (N=250) are being recruited across North America to participate in this RCT that is implemented entirely over the internet. Eligibility criteria include body mass index >25 kg/m2 and > 2 frailty symptoms [illness, fatigue, inactivity, weakness, slowness]). Consented participants undergo assessments that include: online surveys (medical status, falls, physical activity, quality-of-life, healthcare utilization); dietary recalls (kilocalories, diet quality); body weight (Aria® scales); physical activity (Fitbits®); 4) internet-based physical performance (chair stand, timed up-and-go, gait speed tests); and 5) muscle mass (D3 creatine dilution). Participants are then randomized to one of two 6-month interventions: 1) Enhanced Usual Care (EUC): Encouraged to continue Aria® scale and Fitbit® use with monthly emails of publicly available diet- and exercise-related information; or 2) iLIVE: Same as EUC, plus website access to weekly serialized sessions on weight loss and diet quality and thrice-weekly live remote supervised group resistance training sessions. Assessments are repeated at 6-months; at 12-months, questionnaires are repeated and data from digital devices are captured. Intent-to-treat analysis will compare EUC vs. iLIVE (baseline-to-6-months) using a composite measure of obese frailty as the primary outcome. Designed as a type I hybrid-effectiveness implementation trial, data on intervention feasibility (including safety), acceptability, adoption, appropriateness, fidelity, sustainability, and cost are assessed, tracked, and analyzed.

**Discussion:**

The iLIVE RCT is implemented exclusively over the internet and provides a blueprint for other highly scalable lifestyle interventions with potential for rapid translation into nationwide practice.

**Trial registration:**

ClinicalTrials.gov: NCT06011499 (5.31.2025: https://clinicaltrials.gov/study/NCT06011499).

**Supplementary Information:**

The online version contains supplementary material available at 10.1186/s12885-026-15851-4.

## Background

Approximately 60% of American men age 65 and older have prostate cancer, making it the most common malignancy aside from non-melanoma skin cancer in the nation [1]. Nearly half of these men are prescribed androgen deprivation therapy (ADT) [2]. While ADT is necessary to assure cancer control among men with more progressive disease [3], it comes at a price, specifically, the exacerbation of obese frailty (a condition characterized by high fat mass concurrent with low muscle mass) already prevalent among older adults, and a condition that increases the risk of comorbidity and falls, and that reduces physical functioning and overall quality of life [4–8]. Unfortunately, the prevalence of obese frailty remains high even after ADT is discontinued, further amplifying its impact [8].

While “obese frailty” is an emerging concept, the co-occurrence of the obesity epidemic with the aging of the American population and attendant increases in disability have been noted for decades. In 1994 and in a sample of > 3,000 elders, Galanos et al. [9] noted that the risk of functional impairment was significantly higher among those with body mass indexes (BMI) that were < 21.1 kg/m^2^ (Odds Ratio [OR]: 1.34, 95% Confidence Interval [95% CI: 1.04–1.74]), and even greater among those with BMI’s > 31.0 kg/m^2^ (1.43 [95% CI: 1.10–1.86]. As the American public has become older and heavier, reporting on the problem of sarcopenic obesity (a related condition) has been the focus of a handful of interventional studies [10, 11]. A review by Starr and colleagues suggests that multi-behavior interventions that include both dietary modification to reduce caloric intake and increased exercise (especially multifaceted programs involving aerobic, flexibility, and resistance training) offer the best strategy for managing sarcopenic obesity in the broader population of older adults [12]. Despite the overwhelming need to address obese frailty (which not only encompasses the body composition changes inherent with sarcopenic obesity, but also the resulting insult to physical functioning) in special high-risk clinical populations, such as prostate cancer patients on ADT, as well as the population at large, there is a dearth of scalable interventions - interventions that are safe, efficacy-proven, expertly led, and which can be scaled broadly with fidelity to meet the growing needs in this nation.

This paper describes the intervention and the methods of the Internet-Based Lifestyle Intervention to Eradicate Obese Frailty in Prostate Cancer Survivors (iLIVE) Randomized Controlled Trial (RCT). This National Cancer Institute-supported trial is a collaborative effort between investigators at the Oregon Health and Science University (OHSU) and the University of Alabama at Birmingham (UAB). iLIVE is currently enrolling hundreds of men across the country to test the impact of a 24-week web-based intervention that was adapted from a live remote supervised group resistance training program [13], and tested in the GET FIT Prostate trial [14], and then combined with a serialized, web-based diet (weight loss) intervention tested in the AiM, Plan, and act on LIFestYles (AMPLIFY) trial [15]. The primary aim of the iLIVE RCT is to compare the combined resistance training and weight loss intervention to enhanced usual care (i.e., an arm receiving identical self-monitoring devices and access to publicly-available physical activity and diet information) on obese frailty, with secondary aims to explore between-arm differences regarding individual components of obese frailty (e.g., body weight, muscle mass, fatigue, slowness, weakness, and inactivity) and intervention implementation outcomes (e.g., feasibility [including safety], acceptability, cost, sustainability), and to investigate potential effect modifiers to identify those men who benefit the most from the iLIVE intervention. A unique feature of iLIVE is that all components are delivered and assessed fully through remote means.

## Methods/design

### Design and settings

iLIVE is a 2-arm, single-blinded RCT that relies on a single Institutional Review Board Protocol administered by the OHSU Knight Cancer Institute (25281) with approval by UAB (300011042). Designed with the anticipation that, if found acceptable and effective, iLIVE could progress to future larger-scale implementation effectiveness trials, the RCT was designed under a Type I Hybrid Effectiveness-Implementation framework that simultaneously assesses intervention effectiveness and implementation factors [16]. iLIVE is registered on ClinicalTrials.gov (NCT06011499) and is being conducted throughout North America. Active solicitation via physician referral, patient portal prompts and letters of invitation with telephone follow-up are underway at OHSU (and through their liaison with the Oregon State Cancer Registry) and UAB, with nationwide outreach conducted through national and regional prostate cancer support groups, as well as a study website (https://ilive4health.org/welcome). Since all study activities occur online, men can be recruited from anywhere across the continent through various strategies, but all consenting is conducted electronically by the OHSU study team. Signed informed consent (in which the risks of dietary modification and physical activity are detailed, and participants acknowledge these risks and assume potential related-costs) is obtained from all trial enrollees prior to data collection via Adobesign^®^ (San Jose, CA); study ID numbers that assure that the collection of data is deidentified are assigned at that time.

### Eligibility

Men expressing interest in trial participation are screened via telephone by iLIVE study staff to assure that the following eligibility criteria are met: (1) age 18 and above; (2) diagnosed with prostate cancer with completion of radiotherapy, chemotherapy and/or surgery; (3) received > = 6 months of ADT any time in the past 10 years; (4) BMI: 25-<50 kg/m^2^ (with no evidence of unintentional weight loss of > 5% within the last year); (5) not currently engaging in a structured diet or resistance training exercise program; (6) absence of health conditions that potentially affect weight, ability to pursue moderate physical activity, and/or the ability to participate in the intervention or its assessments (e.g., Cushing’s syndrome, uncontrolled hyper/hypo-thyroidism, debilitating stroke, another active invasive malignancy; not fluent in English); and (7) willingness to be randomized and participate fully in the RCT. Men who have yet to finish their primary treatment are placed on a waitlist and activated upon completion, and because muscle mass is being assessed via the D3 creatine dilution method [17], men taking creatine supplements are instructed to pause them for one month before undertaking baseline and 6-month assessments in order to be considered for the trial. Healthcare providers for all potential enrollees are contacted to confirm diagnosis and ADT history. Individuals who meet al.l criteria are then scheduled for a videoconference assessment to assure that their home internet is sufficient for intervention delivery and assessment; and to gather further evidence of frailty by meeting three or more criteria of the Fatigue, Resistance, Ambulation, Illnesses, & Loss of Weight (FRAIL) scale unrelated to weight, i.e., self-reported fatigue, inactivity, or illness and/or prolonged completion (compared to age-related norms) of objective performance testing of the 5-repetition chair stand and the 4-meter walk that suggest weakness or slowness [18], respectively.

### Measures

Individuals deemed eligible are then scheduled for a video conferenced baseline appointment and express mailed the following supplies: (1) a Wi-Fi-enabled Aria^®^ scale and Fitbit Inspire 2 (Google, LLC, Mountain View, CA)(to assess body weight and physical activity); (2) a 30 mg capsule of D3 creatine and urine test strip (to assess muscle mass); and (3) printed instructions. Other equipment needed for online testing (e.g., tablet, webcam, Bluetooth speakers) is included as needed on a case-by-case basis. Participants are emailed links to assist with Fitbit^®^ and Aria^®^ scale set-up (https://360.articulate.com/review/content/994b1496-5e1b-44ac-86ab-0bc1831c5c02/review) and YouTube video instructions for D3 creatine assessments (https://www.youtube.com/watch?v=xP9JnG3qosY&t=1s). Participants also are encouraged to call the study office upon receipt of the package so that a staff member can review the materials, answer questions and facilitate the connection between the scale and Fitbit with the Fitabase database that is managed by study staff. All study databases used by this trial are only accessible by staff members who have completed human subjects training and are password protected and managed behind secure firewalls. All data (except Fitabase and D3 creatine-related data) is logged directly into REDCap^®^ (Nashville, TN) for which the programming assures minimization of missing data and out-of-field observations. All study assessors are trained and blinded with regard to the study condition.

At baseline, participants complete an online survey to report or verify demographic and health data including age, race, ethnicity, income, years of education, marital status, and height (which is assumed to stay constant over the study period). The Charlson Comorbidity instrument also is embedded within this survey [19]. Additional data are collected at baseline and 3-, 6- and 12-month follow-up (with the 6-month follow-up serving as the primary timepoint). See Fig. 1 that depicts study flow.

**Fig. 1 Fig1:**
[figure not shown]
iLIVE study design and flow diagram Legend: The intention-to-treat analysis will use all data from randomized participants who are not excluded due to death or the development of other serious subsequent conditions that affect body weight and function

### Primary outcome

A reduction in the Obese Frailty Phenotype (OFP) score serves as the primary outcome and it is defined as clinically significant weight loss of 5% AND clinically meaningful change in 2 or more frailty components, i.e., weakness, slowness, fatigue, inactivity, and/or illness (see below). The OFP is a dichotomous binary score that indicates improvement when both elements are met (yes) or not (no).

#### Body weight

The Aria^®^ scale directly relays data on each participant’s body weight throughout the study period. Email reminders encourage each participant to weigh themselves (in the morning, without shoes and in light clothing) throughout the study and weights are explicitly taken during the time of video conference assessments. A weight loss of *≥* 5% from baseline to 6-months is considered clinically significant weight loss (see criterion #1 above) [20], and contributes to the OFP composite score.

#### Physical inactivity

As with the Aria^®^ Scale, the Fitbit^®^ also relays data continuously throughout the study period; kcal/week spent in moderate-to-vigorous physical activity (MVPA) is captured at baseline, 3-, 6-and 12-month follow-up timepoints. In addition, the widely-used, Community Health Activities Model Program for Seniors (CHAMPS) physical activity questionnaire is administered online at identical timepoints [21]. For both objective and subjective measures a cut point of *≥* 383 kcals of MVPA/ week will signal an absence of frailty (and will be used in calculating the OFP score); however, in instances in which a discrepancy occurs, results from the self-report will used [21].

#### Sarcopenia

The D3 creatine dilution method, as implemented and analyzed in the Osteoporotic Fractures in Men (MrOS) study [17, 22], will provide data on muscle mass. Participants will ingest a 30 mg D3 creatine capsule and then urinate on a test strip on the second void upon waking and after at least a 12-hour fast, 3–6 days later. Test strips from baseline and 6-month follow-up will be stored in the participants’ freezer until collection at 6-months (either through staff pick-up or via express mail using chilled biospecimen protocols). Given the complex logistics which require additional mailing, staff follow-up (i.e., reminder calls to ingest the capsule and then use the test strip in a fasting state), participant burden, and expense, this measure is only conducted at baseline and 6-months. A cutoff of *≥* 10.75 kg/m^2^ is suggestive of the absence of moderate sarcopenia [23], and hence the absence of frailty for the OFP score (above).

#### Weakness

A timed 5-repetition chair stand time of < 12 s is reported as significantly reducing the risk of falls by roughly 58% [24], thus suggesting the absence of frailty and a factor taken into account in the OFP score (above). This measure will be performed remotely at baseline, 3- and 6-months using a protocol with established excellent intra-rater reliability, i.e., (Intra Class Coefficients [ICC] = 0.92, 95% Confidence Interval [CI] 0.84–0.96) [25].

#### Slowness

As with weakness, this component of frailty (i.e., 4-m walk) will be measured remotely at baseline, 3- and 6 months using a protocol in which the established intra-rater reliability is good, i.e., ICC: 0.87, 95% CI 0.71–0.94 [25]. Usual gait speed will be assessed twice at each timepoint with the fastest observation recorded for subsequent analysis. Values *≥* 1.0 m sec^− 1^ will be viewed as an absence of frailty for the OFP score (above), as comparable gait speeds have been reported as protective in association with falls and a loss of independence [26].

#### Fatigue

This construct of frailty will be measured online via self-report at baseline, 3-, 6- and 12-months using the 4-item Short Form 36 (SF36) vitality subscale [27]. Scores of *≥* 50.00 (normed) will be used for participants aged 50–64 years or scores *≥* 40.00 (normed) will be used for those aged 65 + years as indicating a non-frail state (and used for the OFP score) [28].

### Secondary outcomes

#### Additional measures of physical performance/function

Select components of the Senior Fitness Battery, i.e., the Timed Up and Go (TUG), a widely-used measure of functional mobility and agility, as well as side-by-side, semi-tandem, and tandem standing balance testing also are performed at baseline, 3- and 6-month follow-up via video, given strong concordance with in-person testing [25, 29]. The balance tests can also be combined with the walk speed and chair stand tests to construct the short physical performance battery which has strong predictive validity for increased risk of disability, nursing home admission, and mortality as scores drop below 10 [30]. In addition, the 10-item, SF36 Physical Function subscale is embedded into the online survey at baseline, 3-, 6-, and 12-months [27].

#### Dietary intake

Both calorie intake and diet quality serve as secondary outcomes; hence at baseline and 6-month follow-up, unannounced 2-day diet recalls of 1-weekday and 1 weekend day are collected by a registered dietitian via telephone and entered into the NCI-developed ASA24 [31]. The Healthy Eating Index – 2020 will be used to calculate diet quality [32].

#### Global quality of life

In addition to collecting data on specific subscales of the SF-36, participants also provide online responses to the EuroQol-5 Dimension (EQ-5D) at baseline, 3-, 6- and 12-months: the 5 dimensions are mobility, self-care, usual activities, pain/discomfort, and anxiety/depression. The EQ-5D was chosen as it provides a low burden measure of QOL [33, 34], and can be used to calculate Quality of Life Adjusted Years (QALYs) for the cost-effectiveness analysis.

#### Health care utilization

At baseline, 3-,6-,9- and 12-month follow-up all participants will be asked to report physician and emergency room (ER) visits, and hospitalizations using the instrument of Ritter et al. [35] which demonstrates test-retest reliability 0.76–0.97, low discrepancy with provider records, and no variation by demographics or health status of respondents. These data (in addition to QALYs – see above) will be used for the cost analysis.

#### Falls and related injuries

Due to the sarcopenic nature of the study population, falls and their related injuries are measured frequently, i.e., at baseline (retrospectively, with respect to the previous year) and monthly throughout the study period, using monthly fall reports used in previous fall prevention interventions [14, 36].

#### Safety

Participants are encouraged to report adverse events as they occur but are also queried monthly throughout the 12-month study period. The description of the event is collected, along with details on the medical care received, and whether the participant attributed it to exercise associated with either study intervention or whether they attributed it to dietary changes they were undertaking to reduce their caloric consumption, e.g., indigestion due to higher intakes of plant-based foods. These events are reviewed quarterly by the study team who are blinded to arm assignment and who classify events as serious (i.e., life threatening, permanently disabling, and/or resulting in overnight hospitalization) or non-serious, and attributable, possibly attributable, or non-attributable to the intervention. Obvious serious events are evaluated within 72-hours by the trial MPI’s with assistance from co-investigators with certified medical training and reported to the OHSU Institutional Review Board (IRB). All events are reviewed annually by the OHSU IRB, as well as an independent Data Safety and Monitoring Board (comprised of a biostatistician, clinician-scientist, and a patient advocate) to confirm adherence to safety standards and assess any imbalances between study arms. No interim analyses are planned.

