### Implementation outcomes

Because the iLIVE intervention has high potential for scalability and, if proven efficacious, could help substantial numbers of men, the iLIVE trial was designed using a Hybrid Type I Implementation framework [16]. Select evaluation criteria proposed by Proctor et al. [37] informed data collection in the following intervention implementation areas: feasibility; cost; acceptability; adoption; appropriateness; fidelity; and sustainability.

As described under Secondary Outcomes, some measures serve as independent outcomes but also contribute to broader implementation domains. For example, safety is an important independent outcome, but, when evaluated along with process data gathered on intervention engagement (i.e., % of website sessions completed [obtained from website analytics], use of scales and Fitbits^®^ [obtained from Fitabase^®^], and class attendance logs), as well as retention from study tracking, the end result is a more comprehensive evaluation of feasibility. Likewise, health care utilization and QALYs and costs associated with intervention delivery will be used in a thorough cost-analysis to assess cost-effectiveness of the intervention. To evaluate other implementation domains, a combination of quantitative data (from recruitment or tracking databases, website or device analytics, or participant surveys), along with qualitative data (from semi-structured interviews with participant subsamples or stakeholders [health care providers and health system administrators]) provides a comprehensive approach to evaluate other domains. Examples are as follows.

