#### Sustainability

All participants are encouraged to continue with interventions beyond 6-months and their engagement with websites, devices, and in the case of the experimental group continued exercise session attendance, is monitored from 6 to 12 months to gauge sustainability; semi-structured interviews with health care providers and health system administrators provide qualitative data to inform future integration with clinical care.

Semi-structured interviews are conducted over the telephone by trained moderators using interview guides tailored toward the patient subsample or type of stakeholder and using in-depth interviewing methods [38].

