#### iLIVE intervention

The iLIVE intervention is an amalgam of previous interventions that have shown efficacy in improving diet quality and promoting weight loss, as well as increasing physical activity, especially aimed at improving strength and physical function, i.e., resistance training, among cancer survivors. The message library developed for the efficacy-proven Reach-out to Enhance Wellness (RENEW) intervention which was originally delivered via tailored print materials and telephone counseling to 641 breast, prostate and colorectal cancer survivors [41–43], was first adapted for web-use in the Daughters, dUdes, mothers and othErs Together (DUET) trial among 112 cancer survivors and chosen partners [44, 45], as well as the AiM, Plan and act on LIFestYles (AMPLIFY) trial (*n* = 351) [15, 46, 47], both of which confirmed efficacy. The web-based interventions which provide content that is refreshed routinely via tips of the day, weekly interactive sessions (tutorials), features to track dietary behaviors and body weight, and over 100 tools (e.g., meal plans, grocery lists, cooking videos) were adapted exclusively to meet the needs of prostate cancer survivors on ADT. Likewise, previous functional resistance training programs found effective in improving strength and reducing falls in supervised, facility-based group classes [48–50], were adapted to live remote instruction using standard videoconferencing software (e.g., Zoom), and led by a trained instructor who leads the exercises, modifies exercises for safety and tolerance, provides feedback on proper form, and offers encouragement. A second staff member is either online or on call during exercise sessions to assist with videoconferencing issues and/or safety monitoring. The resistance training program starts with several weeks of mobility and stability exercises designed to improve efficiency and safety of functional exercises that are the core of the functional strength training program. These mobility exercises are then integrated into the warm-up moving forward. The functional strength training program consists of a 60-minute session with a 5–10-minute warm-up, 45 min of functional resistance training, followed by a 5–10-minute cool down. The routine set of functional exercises consists of wall-sits, chair stands, step-ups, push-ups, rows, and core (e.g., plank, bird dog, bridge, dead bug) that are done during each session. As with prior facility-based programs, weighted vests are used to provide overload - an innovative method to progressively increase resistance in the lower body to improve musculoskeletal function without safety risks related to balance disruption that can occur with handheld weights. Given that the vest has multiple pockets distributed evenly around the torso with each holding a ½-lb weight, exercise intensity can be adjusted slowly and in an ergonomically efficient and safe way. The volume of resistance training progresses from the low-to-high moderate intensity range over the 24-week intervention using progression outlines in which vest weight (intensity) is gradually increased from 4% to 15% of body weight, while sets increase from 1 to 3 sets of 10–15 reps (as weight increases the rep range will decrease) [36, 48, 51]. Participants login thrice weekly, for 75-minute sessions that open 15 min prior to and after the exercise session to provide men with time and opportunity for personal interactions - a key element that provides valued peer support that can optimize adherence and retention. Social support, along with self-efficacy and reducing barriers to behavior change are key constructs of Social Cognitive Theory [39, 40], which serves as a unifying behavioral framework for both the physical activity and diet-related components of the iLIVE intervention.

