
#### Enhanced Usual Care (EUC)

As with men assigned to the iLIVE intervention, participants assigned to this arm receive the self-monitoring devices described above, as well as links to consensus-driven diet and exercise information in the public domain, such as American Cancer Society’s Guidelines for Cancer Survivors (https://www.cancer.org/health-care-professionals/american-cancer-society-survivorship-guidelines.html), the American College of Sports Medicine’s Moving Through Cancer (https://www.exerciseismedicine.org/eim-in-action/moving-through-cancer/) and the American Institute for Cancer Research New American Plate (https://www.aicr.org/cancer-prevention/healthy-eating/new-american-plate/). Monthly newsletters posting links to this information (identical links which are embedded within the website content that comprises the experimental iLIVE intervention) are provided to encourage trial retention, and to ensure that all trial participants receive the standard of care for lifestyle factor guidance in accordance with recommendations of the American Society of Clinical Oncology and the National Comprehensive Cancer Network [52–54].

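### Minor adverse events may be detected more often in iLIVE than in EUC, because spontaneous reports and monthly queries are reviewed as one set and only iLIVE men attend live sessions

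*Protocol article*

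**What the plan says.** The Safety section, under Secondary outcomes, sets up two routes by which an adverse event becomes known: "Participants are encouraged to report adverse events as they occur but are also queried monthly throughout the 12-month study period". For each event it lists a description, the medical care received and the participant's own attribution. The route by which the event was reported is not on that list.

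The section then treats the reports as one body. "These events are reviewed quarterly by the study team who are blinded to arm assignment", and they classify seriousness and attribution. All events go each year to the IRB and to an independent monitoring board, "to confirm adherence to safety standards and assess any imbalances between study arms". Under Implementation outcomes the article says that "safety is an important independent outcome" and that it also feeds the feasibility evaluation.

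Contact differs by arm. In the iLIVE intervention section, "Participants login thrice weekly, for 75-minute sessions that open 15 min prior to and after the exercise session", led by an instructor who adapts exercises for safety. "A second staff member is either online or on call during exercise sessions to assist with videoconferencing issues and/or safety monitoring". The EUC section describes devices, links and "Monthly newsletters posting links to this information", with no live sessions. Under Sustainability, iLIVE men's "continued exercise session attendance, is monitored from 6 to 12 months to gauge sustainability", so the difference in contact can persist after month 6.

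**The concern.** The monthly query gives both arms the same chance of detection. The between-query route does not, because an iLIVE man sees staff several times a week and can mention a sore shoulder or be seen to strain something. An EUC man has to initiate the report himself. Unless the query finds everything, the extra route adds events mainly in iLIVE. Blinded classification cannot correct this, since reviewers cannot classify an EUC event that nobody reported.

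What is at stake is how non-serious events are read, particularly the strains and minor injuries that a resistance programme might cause. The board could see an excess that is only better detection, or could dismiss a real excess as better detection. Without the source of each report, the two cannot be told apart. The same counts enter the feasibility conclusion.

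**Working it through.** The article gives no adverse event rate, query sensitivity or safety figure, so there is no stated figure to reproduce. The sample size concerns the primary outcome and is not affected.

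**Contact, from the article.** 3 sessions per week × 24 weeks = 72 scheduled sessions in iLIVE and 0 in EUC. The monthly query is the same in both arms.

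**Model (all capture values assumed).** Let q be the probability that the monthly query detects an event, equal in both arms, and s the probability that it is reported or observed between queries. If the two routes act independently, capture = 1 − (1 − q)(1 − s). With equal true risk, the apparent risk ratio is capture in iLIVE divided by capture in EUC.

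**Main illustration, s = 0.10 in EUC and 0.50 in iLIVE**

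- q = 0.50: (1 − 0.50 × 0.50) / (1 − 0.50 × 0.90) = 0.75 / 0.55 = 1.36
- q = 0.70: (1 − 0.30 × 0.50) / (1 − 0.30 × 0.90) = 0.85 / 0.73 = 1.16
- q = 0.90: (1 − 0.10 × 0.50) / (1 − 0.10 × 0.90) = 0.95 / 0.91 = 1.04
- q = 1.00: 1.00 / 1.00 = 1.00

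**Range over s**

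| s in EUC / iLIVE | q = 0.50 | q = 0.70 | q = 0.90 |
|---|---|---|---|
| 0.05 / 0.20 | 1.14 | 1.06 | 1.02 |
| 0.10 / 0.50 | 1.36 | 1.16 | 1.04 |
| 0.10 / 0.70 | 1.55 | 1.25 | 1.07 |

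In absolute terms, take a true risk of 30% in both arms, q = 0.80 and s = 0.10 against 0.50. Capture is 0.82 in EUC and 0.90 in iLIVE, so the observed risks are 24.6% and 27.0%.

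**Does comparing only query-elicited events remove the problem?** If men answer the query equally in both arms and repeat what they have already reported, capture is q in each arm and the ratio is 1.00 for any q. If a fraction r of already reported events is not repeated, query capture becomes q(1 − r·s). The ratio is then (1 − 0.50r) / (1 − 0.10r), in which q cancels:

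- r = 0.25: 0.875 / 0.975 = 0.90
- r = 0.50: 0.75 / 0.95 = 0.79
- r = 1.00: 0.50 / 0.90 = 0.56

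A query-only comparison can therefore err in favour of iLIVE unless the query explicitly asks for events already reported.

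**The case against.** The strongest reply is that the article shows no bias. It states no pooled analysis and no formal between-arm test of adverse events. Looking for imbalance is a board's oversight task, and a source field or a split table may well exist in the full protocol, the case report form or the analysis plan. Both arms are encouraged to report events as they occur, and the equal monthly query is the usual safeguard. This stands in part. A reader might infer that the safety comparison is biased against iLIVE as a matter of fact. The article does not support that: it shows unequal opportunity and a common review, from which a risk follows. What remains is that source has to be recorded when the event is reported, since an analysis plan cannot separate the routes afterwards. If the full protocol already records it, the sponsor need only confirm this.

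Three further limits also stand.

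- **Contact is not reporting.** A reader might compute (72 + 6) / 6 = 13 times as much contact over 24 weeks. That counts each exercise class as an adverse event query and assumes full attendance. Over 12 months with no later attendance it is (72 + 12) / 12 = 7. Nothing in the article says that class staff elicit or log adverse events, and the second staff member may only be on call.
- **Zero spontaneous reporting in EUC is too strong.** With s = 0 in EUC and 0.50 in iLIVE, the ratios would be 0.75/0.50 = 1.50, 0.85/0.70 = 1.21 and 0.95/0.90 = 1.06. The Safety section's encouragement to report is not limited to one arm, so these are upper values for that iLIVE capture.
- **Falls and serious events are less exposed.** Falls and related injuries have their own monthly reports, and all participants are asked about hospitalizations and emergency visits at fixed times. No difference between arms is stated for either.

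**Conclusion.** The point holds as a risk of unequal ascertainment, confined mainly to non-serious events other than falls. It rests on three things the article does state: a between-query reporting route, about 72 scheduled live sessions in one arm against none in the other, and review of all events as one set for imbalance between arms.

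The likely direction is inflation in iLIVE, provided that between-query capture is higher there and the monthly query misses some events. The size cannot be fixed from the article. Under the assumed values it runs from about 2% with a sensitive query and a small gap in capture to about 55% with a poor query and a large gap, and it vanishes if the query is complete. The primary outcome, its analysis and the sample size are untouched. The change is still worth making, because source is easy to record now and hard to recover later.

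**What to change.** 1. Record the reporting source of every event: monthly query, spontaneous report or class-observed. An event may have more than one source.
2. Word the monthly query, identically in both arms, to cover all events since the last query, including any already reported to staff.
3. Base the between-arm comparison of non-serious events on query-elicited events and show the all-source comparison beside it. Tabulate by arm the events known only from spontaneous or class reports, so that none drops out of view.
4. Keep all serious events in the comparison whatever their source.
5. Report response to the monthly query by arm.

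The cost is one extra data field, a split safety table and somewhat fewer events in the query-based comparison. That comparison is free of the detection difference only if men answer the query equally in both arms and repeat what they have already reported, which is why the all-source figures belong next to it. Enrolment is under way, so for events already logged the source may have to be reconstructed or marked unknown.
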